#### Justification of two primary outcomes

2.7.3

Lifestyle intervention trials in people with type 2 diabetes always face the problem that metabolic parameters, weight, and treatment can hardly be evaluated separately as they influence each other. For example, insulin dose decreases following weight loss will diminish the full impact of the weight loss on HbA1c reduction, while in contrast HbA1c reductions can simply be achieved by insulin dose increases without a contribution of the dietary intervention. Hence, as the parameters are interrelated, we believe that besides looking at the HbA1c change, it is also crucial to investigate a composite of weight, glycaemic control and insulin dose reduction. A weight loss of equal or more than 2% would indicate a weight change beyond the daily fluctuation.^24^ An insulin dose reduction of 10% or more is a pragmatic estimate and indicates better insulin sensitivity^25^ and an HbA1c reduction of at least 0.3% would be considered clinically meaningful.^26^

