#### Primary outcomes

2.7.1

‐The impact of intermittent fasting on the glucose metabolism in participants with insulin‐treated type 2 diabetes mellitus assessed by the difference in the change of HbA1c from baseline to 12 weeks.‐The difference in the number of participants achieving a combined end point encompassing a body weight reduction of at least 2%, an insulin dose reduction of at least 10% and an absolute HbA1c reduction of at least 3 mmol/mol (0.3%).

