#### Insulin adaptation

2.8.18

To prevent hypoglycaemia caused by intermittent fasting,^23^ a specific protocol for insulin dose adaptation is used, adapted from Unnikrishnan et al.^34^ 4 weeks prior to the initiation of dietary intervention, participants switch to the same insulin treatment, consisting of glargine U300 as basal insulin and a short‐acting insulin. Insulin U300 is administered in the morning. Participants using premixed insulin receive 70% of their daily insulin dose as glargine U300 whereas participants using basal‐bolus insulin treatment continue on their original basal insulin dose but are switched to glargine U300. Participants who are allocated to the control group continue glargine U300 and prandial insulin as started in the switch phase with dose adjustments when deemed necessary by the treating physician.

Participants in the intermittent fasting group continue the same treatment as during the switch phase on the eating days and reduce the basal insulin by 20% on the fasting days with no prandial insulin. In case the blood sugar falls below 3.9 mmol/L, the fast is broken, and the glargine U300 dose is reduced by another 10% (on fasting and eating days) for the remainder of the study. (Table 1) Within the insulin switch phase, we standardise the insulin regimen but aim to sustain glucose control from screening without significant intensification of glucose control. During the intervention phase on days with 0% calorie restriction, we aim for 5.6–7.2 mmol/L in the fasting state and <11.1 mmol/L2h postprandial (for detailed insulin dose adjustments, see Table 2). Participants already using glargine U300 are able to start the intervention 7 days ±1 after the screening visit if treatment is stable at the discretion of the treating physician.

**TABLE 1 dme14813-tbl-0001:** Insulin regimen

	Eating days	Fasting days
Control group	Continue insulin dose from switch phase	Not applicable
Intermittent fasting group	Use insulin dose from switch phase	20% basal insulin reduction, no prandial insulin

**TABLE 2 dme14813-tbl-0002:** Insulin dose adjustment on fasting days and eating days

Fasting days	
<3.9 mmol/L	Fast stopped and additional 10% reduction of glargine U300 dose (on fasting and eating days), intake of 24 g of carbohydrates
3.9–5.5 mmol/L	Regular monitoring of glucose level trend
5.6–7.2 mmol/L	Target range
7.3–13.9 mmol/L	Regular monitoring of glucose level trend

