>13.9 mmol/L	4 units of rapid acting insulin bolus and contact site for further insulin adjustment
Eating days	
Pre‐prandial 5.6–7.2 mmol/L	Target range – no insulin dose change required
Postprandial (2h) <11.1 mmol/L	Target glucose – increase prandial insulin by 2 IE if postprandial glucose is >11.1 mmol/l

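### Section 2.7.3 reads an insulin dose fall of 10% or more as better insulin sensitivity, but if fasting days count in the dose, the fasting arm's dosing rule can produce such a fall by itself

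*Protocol article*

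**What the plan says.** Section 2.7.1 makes a dose reduction of at least 10% one of three components of the second primary outcome, beside weight loss of at least 2% and an HbA1c fall of at least 3 mmol/mol. Section 2.7.2 lists the change in insulin dose at 4, 8 and 12 weeks as secondary outcomes. Section 2.7.3 gives the dose component its meaning: "An insulin dose reduction of 10% or more is a pragmatic estimate and indicates better insulin sensitivity".

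Section 2.8.18 sets the doses. After the switch phase, fasters keep their dose on eating days but "reduce the basal insulin by 20% on the fasting days with no prandial insulin". Section 2.8 fixes the fasting days as Monday, Wednesday and Friday. Controls continue the switch-phase dose, adjusted when the treating physician thinks it necessary. A glucose value under 3.9 mmol/L in a faster ends that day's fast and brings a lasting cut: "the glargine U300 dose is reduced by another 10% (on fasting and eating days) for the remainder of the study". Table 2 also works in the other direction: above 13.9 mmol/L on a fasting day it orders "4 units of rapid acting insulin bolus and contact site for further insulin adjustment".

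**The concern.** The dose cut on fasting days is an instruction. It starts with the intervention, applies in one arm only, and is followed whether or not the participant has become more sensitive to insulin. A dose measure that includes those days therefore mixes the instruction with any metabolic response, and the meaning given in section 2.7.3 does not carry over to it.

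The secondary dose outcomes are the most exposed, because no weight or HbA1c condition is attached to them. A difference between arms there could be the dosing rule, reported as improved sensitivity. In the composite, one of the three components would be partly or wholly met by prescription in fasters and not in controls.

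**Working it through.** **The plan's own figure.** The composite is sized at 20 per arm for 10% versus 50% with power 0.80. The usual two-proportion formula without continuity correction gives 20 per arm, and power 0.813 at that size. No stated number is wrong. The issue is what one component measures.

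**Inputs.**
- Fasting days: 3 of 7 (section 2.8).
- Fasting-day dose: 80% of basal, no prandial insulin (section 2.8.18, Table 1).
- Basal share of total dose, b: not given for basal-bolus users, so assumed over a range. For premix users the article says: "Participants using premixed insulin receive 70% of their daily insulin dose as glargine U300". That makes b about 0.7 if the other 30% is given as prandial insulin, which the article does not state.
- Baseline: taken as the switch-phase dose, as Table 1 suggests.
- Adherence limit: 75% of fasting days (section 2.8.20). This is defined on calories. I assume that insulin follows, with the eating-day dose taken on the remaining days.

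**Prescribed fall, eating-day dose unchanged.** With the eating-day dose set to 1, the fasting-day dose is 0.8b. The weekly mean falls by 1 - (4 + 3 x 0.8b)/7 = 3/7 x (1 - 0.8b). If 75% of fasting days are kept, multiply by 0.75.

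| b | All fasting days | 75% of fasting days |
|---|---|---|
| 0.5 | 25.7% | 19.3% |
| 0.7 | 18.9% | 14.1% |
| 0.9 | 12.0% | 9.0% |
| 1.0 | 8.6% | 6.4% |

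The fall reaches 10% when b is at or below (1 - 0.1 x 7/3)/0.8 = 0.958 with all fasting days kept, and at or below 0.861 at 75%. The prescribed fall in controls is 0%.

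**Offsets.** Take 30 IU/day as an illustration (the 0.3 IU/kg entry minimum at an assumed 100 kg).
- A 4-unit bolus on all three fasting days takes back 3 x 4/(7 x 30) = 5.7 points. At b = 0.7 this leaves 18.86 - 5.71 = 13.1%. At b = 0.9 it leaves 12.0 - 5.7 = 6.3%.
- With 75% of fasting days kept, 2.25 days a week, the bolus takes back 2.25 x 4/(7 x 30) = 4.3 points. At b = 0.7 this leaves 14.14 - 4.29 = 9.9%, just under the threshold. Doubling the daily dose halves the amount taken back.
- Eating-day titration also counts against the fall. At b = 0.7 with all fasting days kept, the eating-day total would have to rise by (18.86 - 10)/(4/7) = 15.5% to bring the fall down to 10%.

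**Eating-day dose only.** The Table 1 cut drops out. The lasting glargine cut after a low glucose remains and lowers the eating-day dose by 0.10 x b: 7% at b = 0.7 and 10% at b = 1.

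**The case against.** The strongest reply is that the article does not define the dose measure, and a condensed article may leave that to the full protocol or analysis plan. If the measure is eating-day dose, the Table 1 cut never enters. That stands, and it is why the point is conditional. It does not dispose of the point, because section 2.7.3 states its reading without limit and that reading fails for any measure that includes fasting days.

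A second reply is that diet and dosing rule together are the randomised package, so a dose difference is a valid effect of the package. That is also right. Only the label of insulin sensitivity is in dispute. A reader might go further and infer that fasters meet the component with unchanged insulin need. The article does not support this: intake on fasting days is limited to a quarter of recommended calories, so need on those days plausibly falls.

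A reader might also infer that the composite no longer protects against the problem named in section 2.7.3, that "HbA1c reductions can simply be achieved by insulin dose increases without a contribution of the dietary intervention". That does not follow either. A faster whose eating-day insulin rises must still show a 10% lower dose overall on an all-days measure, and the Table 2 increases make that harder to reach.

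Finally, controls' doses may be lowered by the physician, and the lasting glargine cut answers a measured low glucose. Both are fair. Yet the size and permanence of that cut are set by rule, and a low glucose on a day of severe calorie restriction does not by itself show better sensitivity.

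**Conclusion.** The point holds in a limited form. With fasting days counted and all of them kept, the dosing rule alone takes the weekly dose past the 10% threshold for a basal share up to about 0.96. At the adherence limit this holds up to about 0.86. With basal insulin only, or with lower adherence and regular correction boluses combined, the fall can end just below 10%. The sizes rest on an assumed basal share, baseline and daily dose.

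It would be wrong to conclude that the dosing rule creates composite responders: the weight and HbA1c falls are still required, and the composite is tested only after the HbA1c comparison succeeds. What fails is the interpretation of one component, its balance between arms, and any metabolic reading of the secondary dose outcomes. This is a minor point, but cheap to put right.

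**What to change.** Leave the primary component as it is.

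1. Report the secondary dose outcomes on eating-day total daily dose (total daily dose in controls) beside the all-days dose, and add a sensitivity analysis of the composite on the same basis.
2. Give the number of fasters who had the lasting 10% glargine cut, because this lowers their eating-day dose too.
3. Narrow section 2.7.3: do not read a fall in a dose measure that includes fasting days as better insulin sensitivity.

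The cost is some extra analysis and one reworded sentence. Recruitment is complete, so the additions should be labelled as sensitivity or supportive analyses. Dose records must carry dates, which the article does not say they do. Eating-day dose has its own weaknesses: it ignores three of the seven treatment days and may reflect compensatory eating after a fast. It should therefore stand beside the all-days dose and not replace it. Fewer fasters will meet the dose component in that analysis.

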### Intervention and investigations

2.8

The flow chart of the intervention is shown in Figure 1.

**FIGURE 1 dme14813-fig-0001:**
[figure not shown]
Flow chart of the intervention (an optional single follow‐up after 1 year will be added)

46 participants (23 per group) with insulin‐treated type 2 diabetes mellitus are randomly assigned to ‘intermittent fasting’ or ‘control group’, in a 1:1 ratio. Intermittent fasting comprises 3 days (Monday, Wednesday, Friday) of 75% caloric restriction (i.e. only 25% of the recommended calorie intake; this intake is only allowed as breakfast and/or lunch to maintain an 18 hours period of fasting) and 4 days (Tuesday, Thursday, Saturday and Sunday) of 0% caloric restriction (i.e. ad libitum calorie intake) in 1 week.

#### Biobank sampling

2.8.1

Serum and plasma samples are pseudonymized and stored at −80°C in the Biobank of the Medical University of Graz for potential future analyses.

#### Laboratory measurements

2.8.2

Blood samples are obtained at all on‐site visits after a minimum of 8 h of overnight fasting (but should always take place after a normal feed day to ensure result comparability between groups) and processed by the local laboratory using standard methods for routine tests.

Insulin and c‐peptide are measured by chemiluminescence on an ADVIA Centaur system (Siemens Healthcare Diagnostics). Leptin is measured using an ELISA kit (DRG Instruments GmbH). Routine parameters are determined using a cobas^®^ analyzer (Roche Diagnostics).

#### Peripheral blood mononuclear cell analysis

2.8.3

In a subgroup of up to 20 participants, 32 ml of peripheral blood is collected at baseline visit and visit 10 using BD Vacutainer CPT for the isolation of peripheral blood mononuclear cells. Peripheral blood mononuclear cells (PBMCs) will be further analysed using single‐cell sequencing technique in collaboration with the Division of Cardiology at the Medical University of Graz, Austria.

#### Oral glucose tolerance test

2.8.4

Participants are asked to postpone their insulin injection until the end of the oGTT. Insulin, C‐peptide and glucose are measured before (−5), 15, 30, 60 and 120 min after ingestion of 75 g glucose (^®^Glucoral 75 citron, Germania Pharmazeutika). In addition, lipid parameters (total cholesterol, triglycerides, HDL, LDL, free fatty acids) and a routine safety lab are measured. The oGTT is performed after an overnight fast (apart from water) following an eating day (for the intermittent fasting group) and is evaluated by determining the area under the glucose curve.^27^

#### Continuous glucose monitoring

2.8.5

Minimally invasive CGM measurement is performed using the Abbott FreeStyle Libre glucose monitoring device (Abbott Diabetes care). A sensor is introduced through the skin into the subcutaneous fat tissue. The upper arm is the main body location to applicate the sensors which are worn for 16 weeks (4 weeks insulin switch phase and 12 weeks intervention phase) by the participants. The Abbott sensor is factory calibrated and therefore does not require calibration by capillary prick blood. However, participants are instructed to scan the sensor with the corresponding recorder at least every 8 h. CGM data will be collected at on‐site visits.

#### Non‐invasive 24h ambulatory blood pressure monitoring

2.8.6

Participants wear the blood pressure device for a 24‐h period. During this time, the device is programmed to inflate and record blood pressure at pre‐specified intervals (every 15 min during daytime hours and every 30 min during night‐time hours), which provides approximately 50–75 blood pressure recordings during the 24‐h period.

#### Bone densitometry and body composition

2.8.7

Bone density scanning by dual‐energy X‐ray absorptiometry (DXA) is assessed with the GE Lunar iDEXA (GE Healthcare), estimating simultaneously body composition, for example, fat percentage according to the departmental Standard Operating Procedure. Body regions are defined using standard anatomical partitions. Scan areas are analysed to determine lean mass, fat mass, bone mineral density and total body composition.

#### Bioelectrical impedance analysis

2.8.8

The BIACORPUS RX 4000 (Medical Healthcare GmbH) is used to assess body composition. It is a non‐invasive way to examine total body water and body composition by using eight adhesive electrodes and a frequency of 50 kHz.

#### Activity measurement

2.8.9

The MoviSens‐device (Movisens GmbH) consists of a 5.3 × 3 × 2‐cm‐sized body and is fixed with a clip to the right hip. The three‐axial acceleration sensor has a range of ±8 g, a resolution of 12 bit and a sampling rate of 128 Hz. The recognition of different activities is based on the extraction of mathematical and statistical features of the raw acceleration signal. Calculated features are maximum frequency, step count, and the number of mean crossings.

#### Faeces sampling and microbiome analysis

2.8.10

Sampling is performed with two stool collection tubes (Sarstedt), using a stool collector (Süsse Stuhlfänger). Directions for safe and hygienic faecal collection are provided to the participants of the study in words and in pictograms.

Bacterial DNA is extracted from stool samples using the MagNA Pure LC DNA Isolation Kit III (Roche). 16S rRNA is sequenced with next‐generation sequencing technology (Illumina MiSeq) and interpreted by the respective software analysers.

#### Resting metabolic rate

2.8.11

The RMR is a component of energy expenditure that is measured by indirect calorimetry (IC). Participants must rest at least 30‐min after at least 8 h of sleep and after at least 3 h of fasting. The measurements take place for at least 30 min and are performed in standard neutral hospital room temperature. A breath mask is placed over the head of the participant. Oxygen consumption and carbon dioxide production are measured and energy expenditure is calculated by the Weir formula.^28^

#### Sleep (sleep quality and sleep disturbances)

2.8.12

The Pittsburgh Sleep Quality Index (PSQI)^29^ measures self‐reported sleep quality and disturbances during the previous four weeks. PSQI has 19 items and measures 7 components of sleep: subjective sleep quality, sleep latency, sleep duration, sleep disturbance, use of sleeping medication, habitual sleep efficiency and daytime dysfunction.

#### Sleep (sleepiness)

2.8.13

The Epworth Sleepiness Scale (ESS)^30^ is a self‐reported questionnaire that measures daytime sleepiness. The questionnaire consists of eight items with a respondents format 0 = would never doze, 1 = slight chance of dozing, 2 = moderate chance of dozing and 3 = high chance of dozing.

#### Health‐related quality of Life

2.8.14

The EuroQol Questionnaire (EQ‐5D) measures health‐related quality of life. The questionnaire contains five dimensions: mobility, self care, usual activities, pain/discomfort and depression/anxiety.^31^

#### International Physical Activity Questionnaire

2.8.15

The International Physical Activity Questionnaire will be used to measure health‐related physical activity.^32^

#### Psychosomatic Competence Inventory

2.8.16

A questionnaire concerning interceptive awareness and self‐regulatory behaviour in relation to psychosomatic competence.^33^

#### Dietary counselling

2.8.17

Dietary counselling is performed by a professional dietician and general recommendations are given to all study participants according to the recommendations of the German Nutrition Society (DGE) and personal caloric goals based on age and sex are discussed. At baseline, all participants receive one hour of general dietary counselling by a trained dietician. Participants are encouraged to consume a diverse and balanced diet, with three portions of vegetables and two portions of fruits per day (in general and on eating days). There is no restriction on macronutrient intake, but recommendations include the limitation of sugar and salt as well as the encouragement to consume more whole grains, legumes and smaller amounts of meat, dairy and fat. Water and unsweetened coffee and/or tea are suggested as beverages. Simmering food with small amounts of water and fat is encouraged over fried food. Participants are advised to take their time and to slowly eat meals to enjoy their food and encourage satiety. Though all participants have already received nutritional counselling years prior to the study when they initially started insulin therapy, the concept of prandial insulin dose estimation according to the carbohydrate amount eaten is repeated. All participants will have the same number of contacts with the dietician at the on‐site visits and phone visits for questions. 24‐hour emergency support is available to ensure the participants safety.

The participants of the intermittent fasting‐arm are given personal caloric goals for the fasting and eating days. The participants are presented with a couple of sample meals with a maximum of 500 kcal for the fasting days as a support to not exceed the recommended calorie maximum on those days.

#### Insulin adaptation

2.8.18

To prevent hypoglycaemia caused by intermittent fasting,^23^ a specific protocol for insulin dose adaptation is used, adapted from Unnikrishnan et al.^34^ 4 weeks prior to the initiation of dietary intervention, participants switch to the same insulin treatment, consisting of glargine U300 as basal insulin and a short‐acting insulin. Insulin U300 is administered in the morning. Participants using premixed insulin receive 70% of their daily insulin dose as glargine U300 whereas participants using basal‐bolus insulin treatment continue on their original basal insulin dose but are switched to glargine U300. Participants who are allocated to the control group continue glargine U300 and prandial insulin as started in the switch phase with dose adjustments when deemed necessary by the treating physician.

Participants in the intermittent fasting group continue the same treatment as during the switch phase on the eating days and reduce the basal insulin by 20% on the fasting days with no prandial insulin. In case the blood sugar falls below 3.9 mmol/L, the fast is broken, and the glargine U300 dose is reduced by another 10% (on fasting and eating days) for the remainder of the study. (Table 1) Within the insulin switch phase, we standardise the insulin regimen but aim to sustain glucose control from screening without significant intensification of glucose control. During the intervention phase on days with 0% calorie restriction, we aim for 5.6–7.2 mmol/L in the fasting state and <11.1 mmol/L2h postprandial (for detailed insulin dose adjustments, see Table 2). Participants already using glargine U300 are able to start the intervention 7 days ±1 after the screening visit if treatment is stable at the discretion of the treating physician.

**TABLE 1 dme14813-tbl-0001:** Insulin regimen

	Eating days	Fasting days
Control group	Continue insulin dose from switch phase	Not applicable
Intermittent fasting group	Use insulin dose from switch phase	20% basal insulin reduction, no prandial insulin

**TABLE 2 dme14813-tbl-0002:** Insulin dose adjustment on fasting days and eating days

Fasting days	
<3.9 mmol/L	Fast stopped and additional 10% reduction of glargine U300 dose (on fasting and eating days), intake of 24 g of carbohydrates
3.9–5.5 mmol/L	Regular monitoring of glucose level trend
5.6–7.2 mmol/L	Target range
7.3–13.9 mmol/L	Regular monitoring of glucose level trend
>13.9 mmol/L	4 units of rapid acting insulin bolus and contact site for further insulin adjustment
Eating days	
Pre‐prandial 5.6–7.2 mmol/L	Target range – no insulin dose change required
Postprandial (2h) <11.1 mmol/L	Target glucose – increase prandial insulin by 2 IE if postprandial glucose is >11.1 mmol/l

